| Domains                                   | Variables                                                                                                                                                                                                                                                                                                                                                                                                                                                                                                                      |
|-------------------------------------------|--------------------------------------------------------------------------------------------------------------------------------------------------------------------------------------------------------------------------------------------------------------------------------------------------------------------------------------------------------------------------------------------------------------------------------------------------------------------------------------------------------------------------------|
| Baseline Characteristics                  | experience with prior surgery, problems with blood cells, muscle problems                                                                                                                                                                                                                                                                                                                                                                                                                                                      |
| Pre-op variables                          | age, prior GU reconstruction, monogenic stone disease                                                                                                                                                                                                                                                                                                                                                                                                                                                                          |

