| Surgery variables                         | structural renal abnormality, primary clinical indication for surgery, surgery within 24 hours of symptom evaluation, restrictions to OR access                                                                                                                                                                                                                                                                                                                                                                                |
| Imaging variables                         | imaging type, number of stones, stone location, stone size                                                                                                                                                                                                                                                                                                                                                                                                                                                                     |
| Institutional and surgeon Characteristics | number of kidney stone patients evaluated in outpatient clinic during 2018-2019, the importance of patient age in surgeon's surgical decision-making, the importance of family's preference in surgeon's surgical decision-making, the importance of stone size in surgeon's surgical decision-making, the importance of availability of equipment in surgeon's surgical decision-making, surgeon's preference for URS versus PCNL for a 1.5 cm kidney stone, surgeon's preference for SWL versus PCNL for a 2 cm kidney stone |

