|                                                            | Other - not specified  | 2
(2.2)           | 0
(0)                     | 3
(0.3)            | 1
(0.2)                    |
|                                                            | Missing/Unknown        | 1
(1.1)           | 0
(0)                     | 11
(1.2)           | 3
(0.7)                    |
| Pre-presentation ED visit, n (%)                    |                        | 39
(41.9)         | 18
(39.1)                 | 641
(67.8)         | 305
(70.0)                 |
| Structural renal abnormality in treated side, n (%) | Any Abnormality        | 21
(22.6)         | 7
(15.2)                  | 112
(11.8)         | 43
(9.9)                   |
|                                                            | Horseshoe Kidney       | 2
(2.2)           | 0
(0.0)                   | 3
(0.3)            | 0
(0.0)                    |
|                                                            | Malrotation            | 7
(7.5)           | 2
(4.3)                   | 7
(0.7)            | 3
(0.7)                    |
|                                                            | Pelvic Kidney          | 3
(3.2)           | 1
(2.2)                   | 5
(0.5)            | 0
(0.0)                    |
|                                                            | Chronic Hydronephrosis | 5
(5.4)           | 1
(2.2)                   | 25
(2.6)           | 9
(2.1)                    |
|                                                            | Cross-Fused Extopia    | 0
(0.0)           | 0
(0.0)                   | 1
(0.1)            | 0
(0.0)                    |
|                                                            | Complete Duplication   | 0
(0.0)           | 0
(0.0)                   | 1
(0.1)            | 0
(0.0)                    |
|                                                            | Partial Duplication    | 1
(1.1)           | 0
(0.0)                   | 13
(1.4)           | 7
(1.6)                    |
|                                                            | Transplant Kidney      | 2
(2.2)           | 1
(2.2)                   | 3
(0.3)            | 2
(0.5)                    |

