### 2.2 Secondary Objectives (or Aim)

The secondary objective is to compare patients' experiences after URS, SWL, and PCNL. We will assess the immediate (within 7-days +/- 3 days) and delayed (21-days +/- 7-days, 45-days +/- 7-days, and 90 days +/- 30 days) impact of surgery on patient-reported outcomes (PROs) selected by PKIDS patient partners. The PROs include the PROMIS, other questionnaires commonly used in studying the impact of kidney stone disease on health states, and urinary tract symptoms. We will examine HTE by age and sex and identify modifiable surgical techniques that impact these experiences for each surgery. We will also determine unplanned hospitalizations, ED visits, and repeat surgeries for the 3 months following each procedure.

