### Patient Experiences: Overall Treatment Effect.

For PROMIS measures, we will fit weighted linear mixed effects models to test the difference in T-scores after surgery across treatment options for each domain. Separate models will be built for outcomes at 1 week, 3 weeks, 6 weeks, and 3 months after surgery. We will also take advantage of the longitudinal nature of the PROs and fit WLMMs to compare the slopes of the PROs over time and the area under the curve.

Secondary patient experience outcomes, including number of emergency department visits, unplanned hospitalizations, and surgical retreatment will be compared across treatment options using weighted zero-inflated negative binomial regression models.

**SubAim 2a: HTE.** We will examine for HTE with interaction terms between procedure and patient age and procedure and sex to identify associations that differ for subgroups. We will also explore HTE by other patient participant characteristics including, but not limited to, ambulatory status.

**SubAim 2b: Effect modification by procedure-specific techniques.** We will stratify the data by treatments and, within each treatment; we will fit linear mixed effect models to test whether modifiable techniques are associated with patients' experiences for each procedure.

We will evaluate the change in outcomes across PKIDS after knowledge of best practices generated by the above analyses are integrated into clinical care. Our regression models will test differences in both the intercept (average value) and slope (change over time) for outcomes.

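### Pre-presentation ED visit, strongly imbalanced before weighting, is named in neither the propensity list nor the ED-visit model, so URS could look worse on post-operative ED visits with no procedure effect unless listed proxies balance it.

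*Combined protocol and SAP*

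**What the plan says.** Protocol 2.2 makes ED use part of the secondary objective: "We will also determine unplanned hospitalizations, ED visits, and repeat surgeries for the 3 months following each procedure". The analysis is in protocol 6.3.2, under Patient Experiences: Overall Treatment Effect, where the "number of emergency department visits, unplanned hospitalizations, and surgical retreatment will be compared across treatment options using weighted zero-inflated negative binomial regression models". No baseline covariate is named for that model.

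The weights come from propensity scores. The SAP's final list (eTable 1) gives, for baseline characteristics, "experience with prior surgery, problems with blood cells, muscle problems"; for pre-op variables, "age, prior GU reconstruction, monogenic stone disease"; and for surgery variables, "structural renal abnormality, primary clinical indication for surgery, surgery within 24 hours of symptom evaluation, restrictions to OR access". The imaging domain adds imaging type and the number, location and size of stones, and the last domain covers institution and surgeon. None of these is a measure of earlier ED use. The confounder table in protocol 6.3 is open-ended. It names pain at presentation and whether the procedure was urgent or elective, but no ED visit.

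The SAP lets a confounder that is still unbalanced after weighting enter the outcome model. That rule is written for confounders, so a variable outside the list has no stated route in. The SAP's Outcome model section adjusts PROs for their baseline scores. It describes no ED-visit model, so the ED analysis rests on the protocol text.

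eTables 4 and 5 both report the row "Pre-presentation ED visit, n" (%), so the variable exists for all three groups. Protocol 5.1.2 also lists past acute care use among the items that may be taken from the record at baseline.

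**The concern.** A patient who reached surgery through an ED may be more likely to return to one afterwards. If so, and if the groups still differ on this after weighting, the ED-visit comparison partly measures how patients entered care rather than what the procedure did. URS has the highest share with a prior visit, so any such bias would run against URS in both comparisons that involve it.

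Unplanned healthcare encounters are part of Specific Aim 1 in the protocol abstract, and ED visits are in the secondary objective. They are meant to inform families choosing a procedure, so a modest spurious ratio could be read as a real difference in burden.

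**Working it through.** **Inputs from the documents.** Pre-presentation ED visit in the enrolled cohorts: URS 641 of 946 and PCNL 39 of 93 (eTable 4); SWL 75 of 189 (eTable 5).

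**Inputs that are assumed.** RR, the ratio of post-operative ED-visit rates with and without a prior ED visit, given the weighting variables: 1 to 3. Share of the raw gap left after weighting: 0% to 100%. Neither is in the documents.

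**Step 1, reproduce the stated percentages.** 641/946 = 67.8%; 39/93 = 41.9%; 75/189 = 39.7%. All match.

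**Step 2, raw imbalance.** Standardized difference = (pA − pB) / √{[pA(1 − pA) + pB(1 − pB)]/2}.

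- URS v PCNL: gap 25.8 points (95% CI 15.4 to 36.3); 0.258/√[(0.218 + 0.243)/2] = 0.54.
- URS v SWL: gap 28.1 points (95% CI 20.5 to 35.7); 0.281/√[(0.218 + 0.239)/2] = 0.59.
- Primary analytic cohort, URS v PCNL: 305/436 = 70.0% against 18/46 = 39.1%; gap 30.8 points, standardized difference 0.65. The enrolled cohorts are used below because EHR surveillance for ED visits is not confined to the primary analytic cohort.

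**Step 3, ratio expected if the procedures are identical.** Null ratio = [1 + pA(RR − 1)] / [1 + pB(RR − 1)]. Example, URS v PCNL at RR 2 with the full gap: 1.678/1.419 = 1.18. With half the gap left, closed evenly about its midpoint, the shares become 61.3% and 48.4%, and the ratio is 1.613/1.484 = 1.09.

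| Assumed RR | URS/PCNL, full gap | URS/PCNL, half gap | URS/SWL, full gap | URS/SWL, half gap |
|---|---|---|---|---|
| 1 | 1.00 | 1.00 | 1.00 | 1.00 |
| 1.5 | 1.11 | 1.05 | 1.12 | 1.06 |
| 2 | 1.18 | 1.09 | 1.20 | 1.10 |
| 3 | 1.28 | 1.13 | 1.31 | 1.15 |

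With no gap left, every entry is 1.00.

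**Step 4, could the listed proxies close the gap?** Pain was the primary indication in 67.0% of URS, 29.0% of PCNL and 37.6% of SWL patients. Suppose ED entry depended on a pain indication alone, with rate a if pain and b if not. Solving 0.670a + 0.330b = 0.678 and 0.290a + 0.710b = 0.419 gives a of about 0.90 and b of about 0.22. Indication alone could therefore reproduce the whole URS–PCNL gap. The same rates predict 0.376 × 0.90 + 0.624 × 0.22, about 48%, for SWL against 39.7% observed. About 8 points of the URS–SWL gap would then need other proxies, such as ureteral stones (48.3% URS, 13.8% SWL). This shows what is possible, not what happened.

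**The case against.** The strongest reply is that the comparison is weighted. eTable 1 contains close correlates of an ED presentation (indication, surgery within 24 hours, stone location and size), and step 4 shows that they could absorb much or all of the gap. That stands. A reader might infer from the raw percentages that URS will look worse. The documents do not support that, because raw imbalance does not establish bias in a weighted analysis. Post-weighting balance may be displayed in eFigure 4, which is not reproduced in the text available; whether it includes this variable is unknown.

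A reader might also set 0.54 and 0.59 against the SAP's 0.25 limit and call it breached. That does not follow. The limit applies to listed confounders, after weighting, as a standardized difference in medians; the figures here are raw differences in proportions.

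Three further points have force. First, it is an inference that the ED-visit weights would use eTable 1, since the SAP applies that list to stone clearance and PROs, and the protocol's own list is open. Second, the variable may have been dropped deliberately: the SAP removes candidates correlated above 0.4 with a higher-ranked one. But a correlation just over 0.4 leaves 1 − 0.16 = 84% of the variance unexplained, so pruning alone does not ensure balance. Third, the row is an undefined yes/no item that may describe the route of entry for the index stone. It is not a pre-operative count matching the 3-month outcome, so the parallel with PRO baseline scores is loose. It can still be prognostic.

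**Conclusion.** The point holds as a conditional one. A strongly imbalanced, already collected and plausibly prognostic variable is named in neither confounder list nor the ED-visit model, and no balance result for it is visible. URS could look worse on post-operative ED visits with no procedure effect, by a rate ratio between 1.00 and about 1.3.

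The upper end needs both a threefold effect of a prior visit, given the listed variables, and the full raw gap surviving weighting. The lower end applies if either is absent. The documents settle neither. The case is made for ED visits only; extending it to unplanned hospitalizations would need a separate argument. The primary outcome is not affected.

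**What to change.** In protocol 6.3.2, add pre-presentation ED visit (yes/no) as a covariate in the weighted zero-inflated negative binomial model for ED visits, or include it in the propensity model used for that outcome. State which confounder list supplies those weights, and define the variable. Report its standardized difference after weighting for each pair of procedures. If the proxies already balance it, that figure will show it and the added term should change little.

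The cost is a sentence or two and one covariate already tabulated in all three groups. The downside is one more parameter in a model that may have few events, particularly with 93 PCNL patients.

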**URS: ureteroscopy; PCNL: percutaneous nephrolithotomy; PMCA – pediatric medical complexity algorithm.**

|                                           | PKIDS Responding Sites |                         | Non-PKIDS Responding Sites |                         |
|-------------------------------------------|-------------------------------|-------------------------|-----------------------------------|-------------------------|
| Characteristics                    | URS
No. (%)        | PCNL
No. (%) | URS
No. (%)            | PCNL
No. (%) |
| Number of unique patients                 | 1,252                         | 125                     | 2,008                             | 182                     |
| Age at surgery (Mean, Std Dev)            | 15.5, 3.2                     | 15.5, 3.6               | 17.5, 2.9                         | 17, 3.5                 |
| 8 - 11                                    | 194 (15)                      | 23 (18)                 | 143 (7)                           | 20 (11)                 |
| 12 - 15                                   | 343 (27)                      | 30 (24)                 | 297 (15)                          | 26 (14)                 |
| 16 - 18                                   | 433 (35)                      | 37 (30)                 | 582 (29)                          | 48 (26)                 |
| 19 - 21                                   | 282 (23)                      | 35 (28)                 | 986 (49)                          | 88 (48)                 |
| Sex                                       |                               |                         |                                   |                         |
| Male                                      | 497 (38)                      | 60 (50)                 | 724 (36)                          | 87 (48)                 |
| Female                                    | 772 (62)                      | 63 (50)                 | 1,282 (64)                        | 95 (52)                 |
| Race                                      |                               |                         |                                   |                         |
| White                                     | 979 (78)                      | 91 (73)                 | 1,559 (78)                        | 145 (80)                |
| Black or African American                 | 67 (5)                        | <11                     | 159 (8)                           | 15 (8)                  |
| American Indian or Alaska Native          | <11                           | 0                       | <11                               | <11                     |
| Native Hawaiian or Other Pacific Islander | <11                           | 0                       | <11                               | 0                       |
| Asian                                     | 17 (1)                        | 0                       | 17 (1)                            | 0                       |
| Multiple Races                            | 19 (2)                        | <11                     | 24 (1)                            | <11                     |
| Other (not specified)                     | 162 (13)                      | 24 (19)                 | 238 (12)                          | 19 (10)                 |
| Hispanic                                  |                               |                         |                                   |                         |
| Yes                                       | 174 (14)                      | 23 (18)                 | 384 (19)                          | 60 (33)                 |
| No                                        | 1,018 (81)                    | 91 (73)                 | 1,565 (78)                        | 125 (69)                |
| Other (not specified)              | 60 (5)                        | 11 (9)                  | 59 (3)                            | <11                     |
| PMCA Body Region                          |                               |                         |                                   |                         |
| Cardiac                                   | 157 (13)                      | 28 (22)                 | 243 (12)                          | 32 (18)                 |
| Craniofacial                              | 12 (1)                        | <11                     | 11 (1)                            | 0                       |
| Dermatological                            | 57 (5)                        | 17 (14)                 | 61 (3)                            | 23 (13)                 |
| Endocrinological                          | 131 (10)                      | 15 (12)                 | 196 (10)                          | 26 (14)                 |
| Gastrointestinal                          | 193 (15)                      | 46 (37)                 | 215 (11)                          | 40 (22)                 |
| Genetic                                   | 65 (5)                        | 21 (17)                 | 45 (2)                            | 12 (7)                  |
| Genitourinary                             | 149 (12)                      | 35 (28)                 | 168 (8)                           | 46 (25)                 |
| Hematological                             | 95 (8)                        | 15 (12)                 | 87 (4)                            | 16 (9)                  |
| Immunological                             | 79 (6)                        | <11                     | 83 (4)                            | 13 (7)                  |

**eTable 7.** Distribution of Sex of PKIDS Trial Participants at PCORnet Sites That Participate in PKIDS and PCORnet Sites That Do Not Participate in PKIDS

**URS: ureteroscopy; PCNL: percutaneous nephrolithotomy; PMCA – pediatric medical complexity algorithm.**

|                        | PKIDS Responding Sites |                         | Non-PKIDS Responding Sites |                         |
|------------------------|-------------------------------|-------------------------|-----------------------------------|-------------------------|
| Characteristics | URS
No. (%)        | PCNL
No. (%) | URS
No. (%)            | PCNL
No. (%) |
| Malignancy             | 39 (3)                        | <11                     | 64 (3)                            | 12 (7)                  |
| Mental health          | 342 (27)                      | 52 (42)                 | 513 (26)                          | 48 (26)                 |
| Metabolic              | 225 (18)                      | 47 (38)                 | 297 (14)                          | 48 (26)                 |
| Musculoskeletal        | 227 (21)                      | 54 (43)                 | 265 (13)                          | 42 (13)                 |
| Neurological           | 267 (21)                      | 60 (48)                 | 283 (14)                          | 62 (34)                 |
| Ophthalmological       | 125 (10)                      | 31 (25)                 | 112 (6)                           | 25 (14)                 |
| Otolaryngological      | <11                           | 0                       | <11                               | 0                       |
| Otologic               | 61 (5)                        | 12 (10)                 | 59 (3)                            | 11 (6)                  |
| Pulmonary              | 293 (23)                      | 41 (33)                 | 385 (19)                          | 43 (24)                 |
| Renal                  | 782 (62)                      | 90 (72)                 | 1,301 (65)                        | 128 (70)                |
| PCMA Progressive       | 326 (26)                      | 70 (56)                 | 397 (20)                          | 80 (44)                 |

**eTable 8.** Proportion of Participants Undergoing Percutaneous Nephrolithotomy (PCNL) and Ureteroscopy (URS) Whose Difference in Score at 1 Week Exceeded 30% and 50% of the SD of the Patient-Reported Outcome Measure Among All Participants at Baseline

| PRO                                                                                                                                                                                                                                                                                                                                                                                             | Standard deviation of weighted score of study sample at baseline | The proportion of participants whose difference in the score at 1 week exceeded 50% baseline standard deviation, % (95% CI) |                  |                     |
|-------------------------------------------------------------------------------------------------------------------------------------------------------------------------------------------------------------------------------------------------------------------------------------------------------------------------------------------------------------------------------------------------|------------------------------------------------------------------|-----------------------------------------------------------------------------------------------------------------------------|------------------|---------------------|
|                                                                                                                                                                                                                                                                                                                                                                                                 |                                                                  | PCNL                                                                                                                        | URS              | Difference          |
| DVSS † score                                                                                                                                                                                                                                                                                                                                                                         | 4.38                                                             | 37.6 (12-63.3)                                                                                                              | 29.8 (26.1-33.6) | 7.8 (-18.1,33.7)    |
| QUIKSS ‡ score                                                                                                                                                                                                                                                                                                                                                                       | 11.49                                                            | 21.9 (3.3-40.5)                                                                                                             | 42.7 (38.5-46.8) | -20.7 (-39.8,-1.7)  |
| PROMIS Anxiety                                                                                                                                                                                                                                                                                                                                                                                  | 10.91                                                            | 1.2 (0.6-3.1)                                                                                                               | 23.6 (20.2-26.9) | -22.4 (-26.2,-18.5) |
| PROMIS Pain Intensity                                                                                                                                                                                                                                                                                                                                                                           | 9.61                                                             | 28.7 (7-50.3)                                                                                                               | 30.6 (26.8-34.3) | -1.9 (-23.9,20.1)   |
| PROMIS Pain Interference                                                                                                                                                                                                                                                                                                                                                                        | 11.80                                                            | 35.8 (11.1-60.6)                                                                                                            | 34.8 (31.1-38.5) | 1 (-24,26)          |
| PROMIS Peer Relationships                                                                                                                                                                                                                                                                                                                                                                       | 8.47                                                             | 27.7 (2.6-52.9)                                                                                                             | 24.5 (21-28)     | 3.2 (-22.2,28.6)    |
| PROMIS Sleep Disturbances                                                                                                                                                                                                                                                                                                                                                                       | 10.20                                                            | 10.1 (0.0-24.2)                                                                                                             | 30.6 (26.9-34.3) | -20.5 (-35.1,-5.9)  |
| PROMIS Stress Experiences                                                                                                                                                                                                                                                                                                                                                                       | 9.92                                                             | 3.6 (0.0-7.8)                                                                                                               | 22.6 (19.2-25.9) | -18.9 (-24.3,-13.6) |
| † The range of the Dysfunctional Voiding Symptom Score (DVSS) is 0 to 30.
‡ The range of the Questionnaire for Urinary Issues – Kidney Stone Surgery (QUIKSS) is 0 to 56. QUIKSS is comprised of 16 items that used a frequency response scale and a 7-day recall period. Each item was scored from never (0) to always (4). The total score was the sum of the items. |                                                                  |                                                                                                                             |                  |                     |

**eTable 9.** Impact of Percutaneous Nephrolithotomy (PCNL) and Ureteroscopy (URS) on Patient-Reported Outcomes (PRO), by Sex, at 1 Week Following Intervention

| Sex                                                                                                                                                                                                                                                                                                                                                                                                                                                                      | Female                   |                             |                                             | Male                     |                           |                                             |
|--------------------------------------------------------------------------------------------------------------------------------------------------------------------------------------------------------------------------------------------------------------------------------------------------------------------------------------------------------------------------------------------------------------------------------------------------------------------------|--------------------------|-----------------------------|---------------------------------------------|--------------------------|---------------------------|---------------------------------------------|
| PRO                                                                                                                                                                                                                                                                                                                                                                                                                                                                      | Baseline (pre-op) effect | Procedure effect            | Difference in Difference between PCNL / URS | Baseline (pre-op) effect | Procedure effect          | Difference in Difference between PCNL / URS |
| DVSS † score                                                                                                                                                                                                                                                                                                                                                                                                                                                  | 0.67(0.58,0.76)          | -1.18(-2.59,0.22)           | -0.47(-1.87-0.93)                           | 0.67(0.5,0.83)           | 5.55(1.98,9.11)    | 6.19(2.62-9.75)                             |
| QUIKSS ‡ score                                                                                                                                                                                                                                                                                                                                                                                                                                                | 0.37(0.26,0.48)          | -7.47(-12.86,-2.08)  | -3.58(-9.89-2.74)                           | 0.18(0,0.37)             | -3.66(-16.04,8.72)        | -0.5(-16.41-15.41)                          |
| PROMIS Anxiety                                                                                                                                                                                                                                                                                                                                                                                                                                                           | 0.62(0.53,0.7)           | -7.43(-11.78,-3.09)  | -8.95(-13.22--4.68)                         | 0.63(0.52,0.74)          | -2.06(-5.35,1.22)         | 0.97(-2.26-4.19)                            |
| PROMIS Pain Intensity                                                                                                                                                                                                                                                                                                                                                                                                                                                    | 0.26(0.17,0.35)          | -5.74(-11.44,-0.05)         | -0.41(-6.33-5.51)                           | 0.24(0.12,0.36)          | -4.77(-14.78,5.23)        | -2.44(-12.82-7.94)                          |
| PROMIS Pain Interference                                                                                                                                                                                                                                                                                                                                                                                                                                                 | 0.2(0.1,0.3)             | -7.26(-14.43,-0.09)  | -2.91(-11.83-6.02)                          | 0.29(0.19,0.39)          | -3.48(-8.94,1.98)         | 1.36(-8.98-11.7)                            |
| PROMIS Peer Relationships                                                                                                                                                                                                                                                                                                                                                                                                                                                | 0.67(0.58,0.75)          | 0.73(-2.64,4.11)            | 0.75(-3.24-4.73)                            | 0.67(0.55,0.79)          | 3.57(-4.31,11.45)         | 5.07(-1.73-11.88)                           |
